### Data analysis

Descriptive analysis will be utilized to present baseline characteristics. Independent t-tests/Mann-Whitney tests will be employed to compare normal/abnormal quantitative variables between two groups, while paired t-tests/Wilcoxon tests will assess the intervention’s impact on normal/abnormal quantitative variables. Chi-square tests will be used to compare qualitative variables between groups, and Mac-Nemar tests will evaluate the intervention’s effect on qualitative variables. The Kolmogorov-Smirnov test will assess the normality of data distribution for quantitative variables. If needed, other statistical tests like regression models may be applied. Statistical analyses will be conducted using SPSS 22, with a significance level of 5% considered.

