### Specific objectives

To determine and compare the average score of sexual quality of life of wives of men with myocardial infarction before and after the intervention in two groups.To determine and compare the average score of marital satisfaction of wives of men with myocardial infarction before and after the intervention in two groups.

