After preparing the counseling content for each session, we validated the developed content using the Delphi method based on feedback from reproductive health and cardiology experts at Urmia University of Medical Sciences. These experts possessed the necessary knowledge and skills in sexual counseling and essential care for heart patients. We conducted three rounds of questionnaires with a panel consisting of three cardiology specialists and three reproductive health specialists.

Interventions at the Cardiac Rehabilitation Center of Seyed Al-Shohada Hospital will be conducted with the presence of patients suffering from heart attacks and their spouses. The intervention will be in the form of discussions, group consultations, and individual consultations if needed, which will be presented at the end of the session.

The sessions will be managed by researchers who have the necessary skills and knowledge regarding sexual counseling. The topics of each session will be presented to the participants by the researchers. In this regard, the researcher will facilitate and guide the sessions. During the intervention, tools such as pamphlets, PowerPoint presentations, speeches, and couples counseling will be used to enhance the effectiveness of the intervention program.

First, the demographic information form is completed by the control and intervention groups, and then other questionnaires are completed by the women of both groups (pre-test). One month after the end of the intervention, the questionnaires will be completed again by women in the control and intervention groups (post-test).

**Table 1 Tab1:** Contents of counseling sessions based on the CHARMS method

No	The content of the session	Type of consultation
First	With a focus on establishing communication and building trust and collaboration between couples, evaluating the mental, emotional, and physical health of individuals, identifying their sexual problems, informing couples about the session structure and setting goals, educating on the sexual cycle, and familiarizing them with sexual performance and the internal and external organs of men and women. Defining sexual desire, arousal, lubrication, and orgasm, as well as familiarizing them with the sexual response pattern and explaining the physiological changes in men and women during sexual activity, including sexual positions.	Group

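### The data analysis section assigns the intervention's effect to within-arm pre/post tests and fixes no between-arm comparison as the test of the hypothesis

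*Protocol article*

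**What the plan says.** The Data analysis section gives its two families of tests different jobs. For scores, two-sample tests (independent t or Mann-Whitney) are to compare the arms. The effect of counselling is then given to the other family: "while paired t-tests/Wilcoxon tests will assess the intervention’s impact on normal/abnormal quantitative variables". For categorical outcomes the split is repeated: chi-square tests compare the groups, and "Mac-Nemar tests will evaluate the intervention’s effect on qualitative variables". A model that could use the baseline appears only as an option: "If needed, other statistical tests like regression models may be applied". No model, covariate or trigger is named.

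The between-group sentence does not say whether baseline, post-test or change scores are compared. Nor is any comparison named as the test of the research hypothesis. The Sampling and data collection section has the women of both arms complete the questionnaires before the intervention and again one month after it ends. The data for a baseline-adjusted comparison will therefore exist.

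**The concern.** The reason for a control arm is that a before/after change inside the counselling arm mixes any counselling effect with whatever else moves the scores over the same period. Paired t, Wilcoxon and McNemar tests ask only whether scores moved within one arm. The protocol gives the words impact and effect to exactly these tests, and does so twice, so this is hard to read as a slip. A report that follows the section as written could claim an effect of counselling from a change that the controls shared.

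There is also a smaller cost. The between-arm comparison that is listed has no stated outcome quantity and no primary status, and it is not tied to the pre-test. The contrast that randomisation protects is left in a form less precise than the data allow.

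**Working it through.** **Inputs from the protocol (Sample size section).** SDs 2.47 (pre) and 2.28 (post); difference 82.70 − 81.30 = 1.40; 45 couples per arm before the attrition allowance; two-sided 5%; 80% power.

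**Assumed inputs.** The pre-post correlation r is not given; 0.3, 0.5 and 0.7 are used. The drift shared by both arms is not given; a range is used.

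**The plan's own figure.** Variance sum = 2.28² + 2.47² = 5.198 + 6.101 = 11.299. With the printed constant 7.89, n = 7.89 × 11.299 / 1.40² = 45.5. With exact normal quantiles it is 45.25. The stated 45 is reproduced to within rounding. The average SD is √(11.299/2) = 2.377 and the standardised difference is 1.40/2.377 = 0.589.

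**Paired test in the intervention arm when counselling does nothing.**
- SD of the change = √(11.299 − 2r × 2.28 × 2.47) = 2.81 / 2.38 / 1.85 for r = 0.3 / 0.5 / 0.7.
- Noncentrality = drift / (SD of change / √45), referred to a noncentral t with 44 df and two-sided critical value 2.015.
- Example: drift 0.3 SD = 0.713 points, r = 0.5 gives 0.713 / (2.381/6.708) = 2.01, hence 50%.

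Probability that the paired test is significant at 5%, with true counselling effect zero:

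| Shared drift | r = 0.3 | r = 0.5 | r = 0.7 |
|---|---|---|---|
| 0 | 5% | 5% | 5% |
| 0.2 SD (0.48 points) | 20% | 26% | 39% |
| 0.3 SD (0.71 points) | 38% | 50% | 72% |
| 1.40 points (planned difference) | 90% | 97% | 99.9% |

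**Between-arm tests under the same drift.** The drift enters both arm means and cancels in their difference. In a simulation of 20,000 trials (r = 0.5, drift 1.40, 45 per arm), the paired test rejected in 97.1%, the two-sample test on post-test scores in 4.9% and the two-sample test on change scores in 4.9%.

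**Precision of the between-arm test.** Adjusting for the pre-test multiplies the residual variance by 1 − r², so the standardised difference becomes 0.589/√(1 − r²) = 0.617 / 0.680 / 0.825. Power from the noncentral t at 45 per arm:
- unadjusted post-test comparison: 79%
- adjusted for the pre-test, r = 0.3 / 0.5 / 0.7: 83% / 89% / 97%

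These power figures treat women as independent. Counselling is delivered in groups of 8, and any correlation within those groups would lower them; the documents give no value for it.

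**The case against.** **A between-arm test is planned.** This is true. The independent t or Mann-Whitney test is listed, the specific objectives speak of two groups, and both measurements are taken in both arms. A reader might infer that the unadjusted comparison is also distorted by shared drift. It is not: it keeps its 5% level and loses only precision. But it is not named as the test of the hypothesis, while the within-arm tests are expressly given the effect.

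**The pre-test is not thrown away.** A reader might infer that it is. The text does not support that: the paired tests use it, change scores are not excluded from the two-sample tests, and regression is permitted. What can be said is that no baseline-adjusted between-arm comparison is fixed.

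**The size of the drift is unknown.** This also stands. No questionnaire score is an entry criterion, so regression to the mean from selection is not built in. The men are at least six months past infarction, and the scores are their wives'. Re-testing with the same instruments remains possible. The table therefore shows what different drifts would do, not what is expected.

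**A rule of 'significant with counselling, not in controls'.** A reader might infer this rule. The protocol never states it, and no error rate for it is claimed here.

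**Normality testing.** The Kolmogorov-Smirnov choice between tests of means and of ranks is a separate matter and is not part of this point.

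**An analysis plan could settle it.** That would answer silence. Here the protocol itself names the test for the effect, and an unseen plan would have to contradict it.

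**Conclusion.** The point holds as a fault in what the protocol states. Tests that make no use of the control arm are assigned the intervention's effect, and no between-arm comparison is fixed in their place. Even a modest shared drift of 0.2 SD would raise the chance of a significant intervention-arm change from 5% to between 20% and 39%, and a drift as large as the planned difference would make it 90% or more. These figures rest on the protocol's SDs, 45 per arm, and assumed correlations of 0.3 to 0.7.

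The gain from baseline adjustment is secondary. It depends on the same unknown correlation, is modest at r = 0.3 (79% to 83%) and assumes independent women. The validity problem belongs to the within-arm tests alone and does not extend to the unadjusted between-arm test.

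**What to change.** In the Data analysis section, make the primary analysis of each score a between-arm ANCOVA of the one-month post-test total on arm and pre-test total, reported as the adjusted mean difference with its 95% confidence interval. State that conclusions about counselling rest on that estimate alone. Keep the paired t, Wilcoxon and McNemar results as description of change within each arm, and remove the wording that has them assess the intervention's impact or effect.

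The cost is a few sentences. No new data are needed, since both measurements are already planned in both arms, and the model is available in SPSS.

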## Discussion

One challenge faced by post-heart attack patients is sexual activity. Lack of awareness about this issue can lead to problems like rehospitalization, sudden death during sexual activity, and sexual dissatisfaction for both the patient and their partner [5, 6]. After overcoming the heart attack crisis and its treatment, couples aim to address the sexual gaps in their lives. However, they may encounter sexual difficulties, emotional upheavals, and changes in intimacy levels post-recovery. Men may struggle with hidden fears, while women fear that requests for sexual intimacy may be seen as carelessness or misplaced expectations post-illness. This dysfunctional cycle can strain families and couples for years, impacting their sexual quality and marital satisfaction. Therefore, providing sexual education and counseling can enhance their sexual quality of life.

After this study, an improvement in the quality of sexual life and marital satisfaction of men with myocardial infarction can demonstrate the benefits of sexual counseling intervention based on the CHARMS model in enhancing their sexual quality of life. Similarly, negative results can help in designing new strategies. Additionally, these findings can contribute to the content used in future programs and studies.

## Data Availability

Not applicable
